### Trial Time Frame

| Trial Stages               | Time Frame  |
|----------------------------|-------------|
| Protocol Development       | Spring 2018 |
| Ethics Submission          | Fall 2018   |
| Trial Recruitment Phase    | 2019- 2021  |
| Data Cleaning and Analysis | 2022-2023   |
| Publication                | 2023-2024   |

## APPENDICES

### APPENDIX 1: MUSE Trial Study Flow Chart

[figure not shown]

## APPENDIX 2: Site for Application of Cerebral NIRS Probe

Cerebral probe will be placed on the midline position for monitoring rScO2 in preterm neonates. Alternative sites could be on the right or left side of the forehead and away from nevi, sinus cavities, the superior sagittal sinus, subdural or epidural hematomas, or other anomalies such as arteriovenous malformations. There are currently no unit specific guidelines for application of neonatal NIRS sensor probe. As such, NIRS probe will be placed similar to a previous trial at our center which is by using Mepitel, one between the skin and NIRS probe interface to reduce any skin irritation that could be caused due to the sensor probe. If during the course of the study period center specific guidelines are developed for placement of neonatal NIRS probe that will be adopted into the study, then. Probe sites would be assessed regularly for lead related skin irritation as part of the standard of care practice in the NICU.

The normal reference range of rScO2 for preterm infants varies between 55% and 85% and this would be used for the proposed study. Using NIRS derived cRSO2, Cerebral Fractional Oxygen Extraction (CFOE) will be calculated using the following formula.

$$\text{CFOE} = (\text{SpO}_2 - \text{rScO}_2) / \text{SpO}_2, \text{ where}$$

SpO2= peripheral arterial saturation obtained from pulse oximeter

rScO2= Cerebral oxygen saturation obtained from NIRS monitor

Normal range for CFOE = 0.15- 0.33

### **APPENDIX 3: Targeted Neonatal Echocardiogram procedure**

TNE will be performed using the Vivid E90, GE echocardiography machine. All scans will be performed by either a clinician with extensive training in TNE or by advanced trainees under their supervision. The study will comprise the following standardized assessment:

- Left ventricular performance (Contraction in 4- and 5-chamber views, long and short axis view, VTI, LVO, fractional shortening, IVRT, E:A ratio),
- Right ventricular performance (Contraction 4- and 5-chamber views, long and short axis view with RVO, septum deviation),
- Shunts (PDA: Presence, flow pattern, size and peak velocity MR jet velocity, LA/AO ratio; PFO/ASD/VSD),
- End-organ blood flow: MCA Doppler, Descending Aorta Doppler, SMA, Coeliac axis.

All scans will be reported in real time by attending clinicians dedicated to this service. All studies will be archived on expandable storage of the machines, Xcelera Technology, to store the study images. The scans will all be performed according to unit-specific standardized protocols. Follow-up scans to assess treatment response will be performed according to the clinical situation.

TNE assessment will be performed in 10-15 minute assessment. Babies undergoing TNE assessment are usually contained by facilitated tucking, may be comforted by a parent or nurse and occasionally use of 24% sucrose as needed.

## APPENDIX 4: Calculation of VVR Scores and VIS Scores

The VIS is calculated in the following manner:

**VIS = dopamine dose (mg/kg/min) + dobutamine dose (mg/kg/min) + 100 x epinephrine dose (mg/kg/min) + 10 x milrinone dose (mg/kg/min) + 10,000 x vasopressin dose (U/kg/min) + 100 x norepinephrine dose (mg/kg/min)**

For patients on no vasoactive support at the time of blood gas measurement, VIS equaled zero.

The ventilation index (VI) is measured as follows:

**VI = (Ventilator RR) x (PIP - PEEP) x PaCO2 / 1,000**

For patients who were extubated to CPAP at the time of blood gas measurement, VI equaled zero.

For those on High Frequency Ventilation, PIP-PEEP will be replaced by Mean Airway Pressure (MAP) and ventilator RR of 60 (which is the maximum ventilator rate on conventional mechanical ventilation) will be used for the purpose of calculating VI score.

For patients on NIMV, a calculated PIP of 5cmH2O less than the ventilator set PIP will be used to account for attenuation of set ventilator pressures reaching the nares.

The baseline serum creatinine will be subtracted from serum creatinine (Cr) measurement by 72 hours of life which will be labelled ΔCr. For patients in whom 72 hour serum creatinine measurements were less than or equal to baseline, we will record ΔCr = 0. Creatinine will be measured in mg/dL. In our center creatinine is measured in mmol/L. This will be converted to mg/dL to calculate the score as follows:

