## Methods:

### Study Design

Non-Blinded Randomized Control Trial

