## Outcome Measures

### Primary Outcome

The primary outcome would be VVR Score at 7days in both arms.

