## Statistical Plan and Data Analysis:

### Sample Size Calculation for VVR Scores

Assuming 25% reduction in VVR in intervention arm with mean VVR Score of 30 in control arm and 22.5 in intervention arm, sd-15; t test assuming  $sd_1 = sd_2 = sd$ ;  $H_0: m_2 = m_1$  versus  $H_a: m_2 \neq m_1$

Study Parameters:

$\alpha = 0.0500$ ;  $\text{power} = 0.8000$ ;  $\text{delta} = -7.5000$ ;  $m_1 = 30.0000$ ;  $m_2 = 22.5000$

$sd = 15.0000$

Estimated sample sizes:  $N = 128$ ;  $N \text{ per group} = 64$

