### Analysis

All statistical analyses will be performed with the intercooled Stata Version 18.0 (College Station, Texas). All data will be anonymized for analysis and intention to treat analyses will be performed for primary outcome. All the tests will be two-sided (where applicable), and significance will be defined as p-value  $< 0.05$ . Univariate and bivariate analysis will be done to describe the sample. Categorical variables will be compared by Fisher's Exact Test and continuous variables by Student's t-test (two-sided). Logistic and linear regression models will be developed using forward and backward stepwise methods to examine the association between different VVR cut off (95th centile for the entire study cohort and literature derived cut off of  $VVR > 53^{25}$  that is associated with adverse outcomes in neonatal postoperative cardiac patients) and neonatal outcome. ROC curve will be used for the purpose of validation of the VVR Scores in neonates during the neonatal period.

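### The ventilation term of the primary VVR score uses a different scale for each ventilation mode and can go negative on NIMV; it needs a zero floor and one sensitivity analysis

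*Protocol*

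**What the plan says.** The Primary Outcome section states: "The primary outcome would be VVR Score at 7days in both arms". The sample size section plans on this basis: "Assuming 25% reduction in VVR in intervention arm with mean VVR Score of 30 in control arm and 22.5 in intervention arm, sd-15". It arrives at 128 infants, 64 per group. The Study Design section describes a "Non-Blinded Randomized Control Trial".

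Appendix 4 defines VVR as VIS + VI + 10 × ΔCr, so one point of VI is one point of the primary outcome. It gives four rules for VI:

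- **Conventional ventilation:** rate × (PIP − PEEP) × PaCO2 / 1,000.
- **High frequency ventilation (HFV):** "PIP-PEEP will be replaced by Mean Airway Pressure (MAP) and ventilator RR of 60".
- **NIMV:** a calculated PIP, 5 cmH2O "less than the ventilator set PIP will be used to account for attenuation of set ventilator pressures reaching the nares".
- **CPAP:** "For patients who were extubated to CPAP at the time of blood gas measurement, VI equaled zero".

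The same appendix sets ΔCr to zero when creatinine has not risen above baseline. It gives no such floor for VI.

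**The concern.** The four rules do not share a scale. On conventional ventilation, raising PEEP at a fixed PIP lowers VI. On HFV, raising the distending pressure raises mean airway pressure and so raises VI. Of the two non-invasive modes, CPAP is zero whatever the pressure, while NIMV receives a ventilator-type score that can fall below zero.

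In an infant on no vasoactive drug VIS is zero, and the primary outcome reduces to VI plus the creatinine term. Mode at the day-7 gas is settled after randomisation, by staff who know the allocation, and the protocol text contains no rule that standardises it. If mode use differed between arms, part of the difference in mean VVR would come from the scoring convention, and the planned comparison could not separate that part from physiological benefit.

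**Working it through.** **1. The plan's own figure.** For a difference of 7.5, SD 15, two-sided alpha 0.05 and power 0.80, the normal approximation gives 2 × (1.960 + 0.842)² × (15/7.5)² = 62.8, so 63 per arm. The two-sample t-test gives 63.77, so 64 per arm and 128 in total, with power 0.801. The stated size reproduces and is not in dispute.

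**2. Sign of the NIMV score.** Reading the rule with PEEP still subtracted, VI = rate × (set PIP − 5 − PEEP) × PaCO2 / 1,000. This is negative whenever set PIP − PEEP < 5, at any rate and PaCO2. Illustration with assumed settings of 10/6, rate 30 and PaCO2 50: 30 × (10 − 5 − 6) × 50 / 1,000 = −1.5, against 0 on CPAP.

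**3. Size of the NIMV-CPAP step for one infant.** The protocol gives no ventilator settings apart from the HFV rate of 60, so these are assumptions: NIMV 20/6, PaCO2 50.

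- Rate 20: 20 × (20 − 5 − 6) × 50 / 1,000 = 9.
- Rate 40: 40 × 9 × 50 / 1,000 = 18.
- CPAP: 0.

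**4. From one infant to the trial.** Shift in the mean difference = step × between-arm difference in the share of infants on NIMV rather than CPAP.

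| Imbalance (percentage points) | Step 9 | Step 18 | Share of 7.5 |
|---|---|---|---|
| 10 | 0.9 | 1.8 | 12–24% |
| 20 | 1.8 | 3.6 | 24–48% |
| 30 | 2.7 | 5.4 | 36–72% |

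Imbalance needed for the full 7.5 points: 7.5/18 = 42 percentage points, or 7.5/9 = 83.

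**5. Consequence for the test.** SE = 15 × √(2/64) = 2.65. With no true effect, a systematic shift of 1.8 points would raise the two-sided error rate from 5% to about 10%, and 3.6 points to about 27% (normal approximation, SD unchanged). These figures treat the whole shift as artefact, so they are upper illustrations.

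**6. Conventional ventilation against HFV.** Assumed 18/6 at PaCO2 50 gives 18, 24 or 36 at rates 30, 40 or 60 (for example 40 × 12 × 50 / 1,000 = 24). With one-third inspiratory time the mean pressure is 6 + 12/3 = 10, and HFV at that pressure scores 60 × 10 × 50 / 1,000 = 30, inside the conventional range. A wider assumed grid had rates 30–60, PIP − PEEP 8–16, PEEP 5–7, PaCO2 40–60, inspiratory time 0.30–0.35 s, and HFV mean pressure 0–2 above conventional. It gave shifts of −22 to +23, median +3.4, beyond 7.5 in either direction in about 37% of combinations. The change of scale is real, but its direction is not fixed.

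**The case against.** A reader might infer that, because one infant can move by 9 to 18 points, a change of mode outweighs the planned effect. That compares unlike quantities. The 7.5 is a difference between arm means with an SD of 15, and one infant's move biases nothing without an imbalance between arms. None of the scenarios in the table reaches 7.5.

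A reader might also infer that unblinded staff will favour a mode by arm. No text in the protocol says so. Both arms are treated in one unit, the intervention is hemodynamic assessment, and its scheduled elements end by 72 hours. Chance imbalance is already covered by randomisation and the t-test. If better hemodynamic care leads to less respiratory support, that belongs to the stated hypothesis. Several appendix figures are not reproduced, so their content cannot be judged.

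Nor does the score plainly misrank support. NIMV delivers set inflations that CPAP does not, so a higher NIMV score partly reflects more support. An NIMV infant on 20/6 at rate 40 scores 18, and an intubated infant on 16/5 at rate 30 scores 30 × 11 × 50 / 1,000 = 16.5, but the first also has the higher set pressure and rate. The mode rules are prespecified, and the NIMV deduction is supported by a citation.

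All of this stands and limits the point. It does not remove the missing floor, which follows from the formula alone, or the gap between a rule of zero for one non-invasive mode and a ventilator-type score for the other. Negative scores may be rare and small.

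**Conclusion.** The point holds in a limited form. Appendix 4 puts the ventilation term on scales that differ by mode, and it allows a negative NIMV score that ranks below CPAP. Both follow from the text without assumed settings.

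The possible effect on the trial result is conditional. With an assumed step of 9 to 18 points and a 20-percentage-point imbalance in NIMV use, the mean difference moves by 1.8 to 3.6 points, or 24% to 48% of the planned 7.5. That rests on illustrative settings and on an imbalance that the protocol neither predicts nor excludes, and some of the shift would be genuine. This is reason to make the dependence on mode visible, not to discard the score or to expect a biased trial.

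**What to change.** 1. Keep the Appendix 4 formula for the primary score, with VI = max(0, VI).
2. Prespecify one sensitivity analysis of the day-7 comparison in which VI = 0 for all non-invasive support, NIMV and CPAP alike. It ignores a real difference in support, so it serves as a check on the primary score and does not replace it.
3. Tabulate ventilation mode at the day-7 gas by arm. This also shows any imbalance in HFV, which the sensitivity analysis does not address.
4. State in the conclusion whether the result depends on how NIMV is scored.

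A common mean-pressure term with rate 60 for all intubated infants is not advised. It would carry PEEP into every score and enlarge the step at extubation: for 16/5 at rate 30, mean pressure is 5 + 11/3 = 8.7 at one-third inspiratory time, and VI would rise from 16.5 to about 26.

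The cost is a few lines of text, one extra analysis and one table. The downside for the sponsor is that a mode-dependent result would be reported less favourably. No treatment changes.

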Various scoring measures have been used in neonates and children to objectively categorize the cardiovascular support using inotrope use as a surrogate. Vasoactive inotrope score (VIS) which provides a numerical sum of inotrope doses used, has been used in preterm infants to quantify cardiovascular support in the perioperative period . A more comprehensive score: Vasoactive Ventilation Renal Score (VVR) that incorporates ventilation support and renal function assessment has been used to evaluate children during the perioperative period . There are no neonatal studies using VVR Scores in the transitional period after birth.

The hypothesis is that having a detailed hemodynamic understanding using a multimodal assessment will result in better cardiorespiratory and renal health at 1 week in ELGAN as evidenced by lower VVR Scores.

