  - f) The findings will be carefully integrated within the clinical context to reach a description of the hemodynamic status of the study infant ([APPENDIX 5 and 7](#)).
- 4) All neonates will have standardized assessment for lead related skin abrasions as per standard practice, neonatal pain and stress assessment (NPASS Score) as part of their standard care.
- 5) Developmental support care will be given by the support person during the TNE assessment as per standard unit practice.

- 6) The discontinuation of either or both NIRS and TNE will depend on the discretion of the clinical team. The reason for the discontinuation will be sorted. This does not constitute a deviation from the study protocol.
- 7) The admission, 24 hours, 48 hours, 72 hours and 7days mean and median VVR and VIS scores will be calculated in both Study and Standard arms. ([APPENDIX 4](#)).
- 8) Urine output will be monitored during the study period as a surrogate for renal function and urine output less than 1 ml/kg/hr will be considered as oliguria.
- 9) SNAPPE-II Scores, which is a validated disease severity score in preterm babies, will be calculated in both study and standard arm at admission, 72 hours and 7 days of life.
- 10) The study team will be available 24/7 for hemodynamic consultation and for the ease of making hemodynamic interpretation, each pathway in the comprehensive guidelines will be transcribed into individual flash cards that will be easily accessible to study team. ([APPENDIX 8](#)).

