**serum creatinine (mmol/dL) x 0.0113 = serum creatinine (mg/dL).**

Using each of these individual measurements, the VVR Score at the time of each arterial blood gas measurement will be calculated as follows:

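### The renal term of the 7-day primary VVR score is fixed by 72 hours of life, so it cannot reflect renal change between 72 hours and day 7

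*Protocol*

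**What the plan says.** Four places in the protocol bear on this.

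- **Appendix 4, renal term.** This is the only definition of ΔCr: the baseline value is subtracted from the "serum creatinine (Cr) measurement by 72 hours of life which will be labelled" ΔCr. The floor at zero also names that time: "For patients in whom 72 hour serum creatinine measurements were less than or equal to baseline", ΔCr is recorded as 0. No other creatinine time is given.
- **Appendix 4, score.** VVR is VIS + VI + 10 × ΔCr, and "the VVR Score at the time of each arterial blood gas measurement will be calculated as follows". The zero rules for VIS and VI both refer to the infant's state when the blood gas is taken.
- **Study Procedure, item 7, and Primary Outcome.** "The admission, 24 hours, 48 hours, 72 hours and 7days mean and median VVR and VIS scores will be calculated" in both arms, and "The primary outcome would be VVR Score at 7days in both arms".
- **Background, hypothesis.** The multimodal assessment "will result in better cardiorespiratory and renal health at 1 week in ELGAN as evidenced by lower VVR Scores".

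**The concern.** A score reported at 7 days should be built from values that describe the infant at about 7 days. Two of the three VVR terms do so. The third is closed at 72 hours. A renal injury that appears on day 5 adds nothing to the primary outcome, and a creatinine rise at 72 hours that has resolved by day 7 still counts in full. The renal part of the 1-week hypothesis is therefore tested with a value up to four days old.

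A second question concerns the early scores. If the single ΔCr is used throughout, the admission, 24-hour and 48-hour scores contain a creatinine drawn later than the time they claim to describe.

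**Working it through.** **1. The plan's own figure.** Inputs from Sample Size Calculation for VVR Scores: means 30 and 22.5 (difference 7.5), SD 15, two-sided α 0.05, power 0.80. The standardised difference is 7.5 / 15 = 0.5. The t-test calculation gives 63.77, hence 64 per group and N = 128, as stated; power at 64 per group is 0.801. The sample size is not in dispute.

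**2. Timing of each term in the 7-day score (Appendix 4).**

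| Term | When the value is taken | In the 7-day score |
|---|---|---|
| VIS | at the blood gas | day 7 |
| VI | at the blood gas | day 7 |
| 10 × ΔCr | by 72 hours of life | 72 hours or earlier |

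Whether the 72-hour phrase means the value at 72 hours or the latest value up to 72 hours, no later creatinine can enter.

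**3. Effect on one infant's score.** Let Cr0, Cr72 and Cr7 be creatinine in mg/dL at baseline, 72 hours and day 7. The time-matched score minus the score as written is

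10 × [max(0, Cr7 − Cr0) − max(0, Cr72 − Cr0)].

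With both later values above baseline this is 10 × (Cr7 − Cr72):

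| Change after 72 h (mg/dL) | Shift in VVR (points) | Share of SD 15 |
|---|---|---|
| 0.1 | 1.0 | 1.0 / 15 = 0.07 |
| 0.25 | 2.5 | 2.5 / 15 = 0.17 |
| 0.5 | 5.0 | 5.0 / 15 = 0.33 |
| 0.75 | 7.5 | 7.5 / 15 = 0.50 |

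The changes in the first column are assumptions, chosen to show the scale. If neither later value exceeds baseline, the shift is 0. The SD is the right yardstick here, because this is one infant's score and not a difference between means.

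**4. Effect on the comparison.** The difference between arms changes only if the mean shift in step 3 differs by arm; a shift of equal mean in both arms cancels. The protocol has no creatinine data from which to estimate this. Purely as an assumption, suppose the 72-hour rule shrank the between-arm difference by b mg/dL of creatinine, with SD 15 and 64 per group unchanged:

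| b | Difference, 7.5 − 10b | Power |
|---|---|---|
| 0.05 | 7.0 | 0.745 |
| 0.1 | 6.5 | 0.682 |
| 0.2 | 5.5 | 0.539 |
| 0.3 | 4.5 | 0.391 |

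The rule could equally enlarge the difference. The table shows sensitivity and predicts nothing.

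**5. Early scores.** On the literal text, the one ΔCr enters every score, and the floor rule points to the 72-hour measurement. Against that, a limit worded as by 72 hours, together with a score computed at each gas, can be read as the latest creatinine available at that gas. The text does not settle which is meant.

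**The case against.** The strongest reply is that a fixed early renal term may be deliberate. NIRS runs for the first 72 hours and the second scheduled echocardiogram falls at 66–72 hours, so 72 hours closes the intervention window. The Primary Objective centres on inotrope use, which VIS captures at day 7. The rule is the same in both arms, so it does not by itself create a false difference. Each of these facts is correct. But the protocol gives no such rationale for the 72-hour limit, and its hypothesis names renal health at 1 week.

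A reader might infer several stronger things that the documents do not support:

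- *That the primary outcome is not a day-7 score at all.* Only one of its three terms is out of date.
- *That the early scores certainly contain later data.* The wording is ambiguous, as shown above.
- *That the admission score is spoiled as a covariate or balance check.* The protocol plans neither use, and admission severity is measured separately by SNAPPE-II. The 24- and 48-hour scores are not listed under Secondary Outcomes.
- *That a 5-point shift in one infant removes two thirds of the planned 7.5-point effect.* That sets an individual change against a difference in means.

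**Conclusion.** The point holds for the primary outcome. Under any reading of Appendix 4, the renal term of the 7-day VVR excludes creatinine after 72 hours. This conflicts with the stated endpoint time and with the 1-week hypothesis. It is a rule the protocol states, not a detail left to the statistical analysis plan.

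The size per infant is 1 point for each 0.1 mg/dL of change after 72 hours, above the floor, against an SD of 15. The size and direction of any between-arm effect cannot be derived from the protocol, so neither bias nor loss of power is shown. N = 128 stands as computed. For the admission, 24-hour and 48-hour scores, the finding is ambiguous wording that needs settling.

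**What to change.** Reconcile the Background hypothesis, Study Procedure item 7, Primary Outcome and Appendix 4:

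- Define ΔCr at each scoring time as the clinically available creatinine nearest that time, within a stated window, minus baseline, floored at 0. For the primary outcome this is the value nearest day 7.
- Set ΔCr to 0 at admission, and state which creatinine is the baseline.
- State the rule for infants with no value in the window, for example the last available value, and report how many are affected.
- Keep the 72-hour version as a sensitivity analysis.

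The text change is a few sentences in Appendix 4. The real cost is data availability: the protocol does not say that creatinine is drawn near day 7, and Data Collection and Handling does not name it among the first-week data. Availability should be confirmed before the rule is fixed. Some infants may have to rely on an earlier value, and for them the mismatch remains. The proposal needs no extra sampling.
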